### Objectives [7]

The *primary aim* of the study is to investigate the effectiveness of a sensorimotor training intervention (SMART-Treatment, SMART) in contrast to standard therapy (Normal Treatment, NORMT) after an acute first-time LAS on perceived ankle joint function. We hypothesize that patients treated with SMART show a better subjective outcome in perceived ankle joint function than patients treated with NORMT.

The *secondary aim* is to determine an effective test battery for the valid measurement of a functional ankle instability. This will be achieved by comparing injured patients (2 weeks after initial injury, t1, as well as after the training intervention, t2) with an uninjured control group (CONTROL).

While primary aim of the study is studied in a longitudinal manner, the design of the secondary aim of the study can rather be classified as a cross-sectional study. Therefore, both study arms work independent from each other, and each have an own statistical approach.

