#### Secondary study aim

The primary study outcome, CAIT, will be analyzed with an unpaired *t*-test, comparing injured patients with the uninjured control group. The same will be done for some secondary outcome measurements like FAAM, postural control, joint repositioning sense, jump, and strength metrics.

Continuous data (isokinetic measurements, IMU and EMG data of gait, run and jumps, ground reaction forces) will be analyzed via SPM, as described above.

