#### Secondary study aim

Since the secondary study aim is a cross-sectional analysis of t1 and t2, later withdrawal is irrelevant for the analysis. Therefore, analysis will be conducted on an intent-to-treat basis, including data for each participant who was randomized, regardless of whether they later withdraw from the study.

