## Discussion

The study has two main aims which are going to address: The primary aims are to investigate the effectiveness of a sensorimotor training intervention in contrast to standard therapy after an acute LAS on perceived ankle joint function. We hypothesize that patients treated with SMART show a better subjective outcome in perceived ankle joint function than patients treated with NORMT. Since currently, there is a high rate of acute LAS developing a CAI, this study has the potential to improve the healthcare for LAS patients in the long term. The data of this study might therefore be used for a future standardized evidence-based rehabilitation-concept being able to reduce the long-term CAI rate.

The secondary aim is to determine an effective test battery for the valid measurement of a functional ankle instability. This will be achieved by comparing the injured patients with an uninjured control group. Therefore, it might be necessary to not only compare the acute state (t1) with the uninjured control group but also the time point after the intervention (t2). The goal is to identify specific tests which are able to display an abnormal trend of the ankle function. These would then further allow to navigate through LAS rehabilitation of future patients.

Additionally, it might be possible to identify risk factors in the test battery predicting a CAI. Eventually, some patients have a higher probability to develop a CAI. These identified risk factors could then be used to screen patients after the injury and monitor them more closely.

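### The injured-versus-uninjured mean comparisons give known-groups evidence only, not the valid test battery that the secondary aim promises, and as written the t2 comparison would combine SMART and NORMT

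*Protocol article*

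**What the plan says.** Objectives [7] of the protocol article gives the secondary aim as "to determine an effective test battery for the valid measurement of a functional ankle instability". The aim is to be met by comparing injured patients, at t1 (two weeks after injury) and at t2 (after the intervention period), with an uninjured group called CONTROL. The Background motivates it by the lack of a battery that helps to diagnose functional instability.

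The method is in section [20a] under Secondary study aim. CAIT and some secondary outcomes go to an unpaired t-test "comparing injured patients with the uninjured control group". Curve data "will be analyzed via SPM, as described above".

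Section [20c], again under Secondary study aim, sets the analysis population. It calls the analysis a cross-section at t1 and t2, says that "later withdrawal is irrelevant for the analysis", and applies an intention-to-treat label, "including data for each participant who was randomized, regardless of whether they later withdraw from the study".

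The Discussion words the goal more loosely, as finding tests that show an abnormal trend in ankle function. It adds that "it might be possible to identify risk factors in the test battery predicting a CAI".

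**The concern.** There are two difficulties, and both lie in what the article fixes.

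**Aim and method do not match.** A t-test, or SPM on a curve, asks whether two group means differ. Neither says how far the two distributions overlap, which decides whether a test is useful in a single patient. Neither selects tests or combines them into a battery. The contrast itself is recent sprain against no injury. At t1 every patient is within weeks of an MRI-confirmed ligament lesion, so a difference shows the effect of a recent sprain. The Background puts later chronic instability at 25% of sprain patients, so most of the injured group would not be expected to become chronically unstable.

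**The injured group at t2.** By t2 the patients have had six weeks of two different treatments, which the primary hypothesis expects to produce different results. With a single injured group, the t2 deficit depends on the treatment effect and on the 1:1 mix. A test that detects a residual deficit under standard care could be dropped because SMART removed that deficit in the other half of the patients.

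At stake is whether the secondary aim is answered. Tests could enter or leave the battery on p-values that say little about discrimination.

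**Working it through.** The article states no sample size for CONTROL or for the secondary aim, so there is no planned figure to reproduce. What follows is illustrative.

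**Inputs.** Patients: 82 in total, 41 per arm (Sample size [14], before the allowance for loss). CONTROL: 41 assumed, with a range of 20 to 102. Two-sided alpha 0.05, assumed for this aim. Scores are taken as normal with equal SD in each group, and d is the mean difference in SD units.

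**1. What significance says about discrimination**

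- Power of the t-test: noncentrality = d × √(n1·n2/(n1+n2)). For d = 0.5 with 82 versus 41 this is 0.5 × √(3362/123) = 2.61. The critical value on 121 degrees of freedom is 1.98, giving power 0.74. With 102 versus 51 it is 0.83.
- AUC = Φ(d/√2). For d = 0.5, Φ(0.354) = 0.64. For d = 0.8, Φ(0.566) = 0.71.
- Sensitivity at 80% specificity = Φ(d − 0.842). For d = 0.5, Φ(−0.342) = 37%. For d = 0.8, Φ(−0.042) = 48%.

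The smallest observed difference that reaches p = 0.05 is d = t(0.975) × √(1/n1 + 1/n2):

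| Patients vs CONTROL (assumed) | Observed d at p = 0.05 | AUC at that d |
|---|---|---|
| 82 vs 20 | 0.49 | 0.64 |
| 82 vs 41 | 0.38 | 0.61 |
| 82 vs 82 | 0.31 | 0.59 |
| 82 vs 102 | 0.29 | 0.58 |

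An AUC of 0.80 needs d = √2 × Φ⁻¹(0.80) = 1.19, and 0.90 needs 1.81. Whatever CONTROL size is assumed, a test can be significant and still separate individuals poorly.

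**2. Whether the arms are combined at t2**

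Three statements have to be read together. Objectives [7] names one set of injured patients measured at t1 and t2. Section [20a] applies a two-group test. Section [20c] includes every randomised participant. Together they give a single injured group at t2 made up of both arms, and nothing in the article separates them. At t1 this is harmless, because treatment has not started.

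**3. Effect of combining**

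With equal arms, pooled deficit = NORMT deficit − (SMART advantage)/2. For an advantage g, the variance of the pooled patients rises to about 1 + g²/4, which the power figures include. Take a NORMT deficit of 0.8 SD:

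| SMART advantage (SD) | Pooled deficit (SD) | Power, pooled 82 vs 41 |
|---|---|---|
| 0 | 0.80 | 0.99 |
| 0.25 | 0.68 | 0.94 |
| 0.5 | 0.55 | 0.80 |
| 0.8 (full restoration) | 0.40 | 0.50 |
| 1.0 | 0.30 | 0.30 |

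NORMT alone against CONTROL (41 versus 41) has power 0.95 at 0.8 SD. In the third row the SMART deficit is 0.8 − 0.5 = 0.3 SD, and SMART alone against CONTROL has power 0.27.

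**4. Withdrawal**

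A patient who leaves during the six-week programme has no t2 measurement. Later withdrawal therefore cannot affect the t1 cross-section, but withdrawal before t2 does affect the t2 one.

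**The case against.** The strongest reply is that the Discussion sets a more modest goal than the Objectives. If the goal is only to find tests that show an abnormal trend, a difference between injured and uninjured means addresses it, and is a reasonable first screen. That stands, and it is why narrowing the claim is an acceptable remedy. It does not rescue the wording in the Objectives, which promises valid measurement.

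Second, a reader might infer that the article states that the arms are pooled at t2. It does not. Including every randomised patient is compatible with comparing each arm with CONTROL, and the Discussion calls the t2 comparison only possibly necessary. Pooling is what the text yields if followed literally; the fuller documents may differ.

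Third, a reader might fault the plan for failing to predict CAI. Prediction is not a stated objective; the Discussion mentions it only as a possibility.

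Fourth, an AUC on the t1 contrast still compares sprained with unsprained ankles, and under the normal model it is a transform of d. This is correct. The AUC puts the result on a scale that shows overlap between individuals, but does not turn recent sprain into instability. It also does not apply directly to the curve data sent to SPM.

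Fifth, the withdrawal wording is a small matter, since the section can be read as using whatever data exist at each visit. Covariate adjustment and multiplicity control are commonly left to an analysis plan and are not part of this point.

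**Conclusion.** The point holds in two parts. The named analyses give known-groups evidence and cannot by themselves support a claim of valid measurement. At an assumed 82 versus 41, a 0.5 SD difference is significant about 74% of the time with an AUC of 0.64; across assumed CONTROL sizes of 20 to 102, p = 0.05 corresponds to an AUC of 0.64 down to 0.58. As written, the t2 comparison would also reduce a residual NORMT deficit by half the difference between arms.

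The loss from combining is slight for a small treatment effect (0.8 SD becomes 0.68 SD if SMART is better by 0.25 SD) and reaches one half only if SMART restores function completely. These sizes rest on an assumed CONTROL group, assumed deficits, normal equal-variance scores and equal arms at t2. The mismatch between aim and method does not depend on them.

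The randomised comparison of SMART with NORMT is unaffected. The change is worth making because a stated aim would otherwise go unanswered.

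**What to change.** 1. For each single-value test, report the AUC with its 95% CI beside the mean difference, and judge the test on the AUC. Keep SPM for the curves, described as a comparison of group means.
2. At t2, compare CONTROL with SMART and with NORMT separately.
3. In [20c], replace the intention-to-treat label with all participants who have data at the visit concerned, and drop the statement that withdrawal is irrelevant as far as t2 is concerned.
4. State that the t1 contrast shows deficits after a recent sprain. Limit the conclusion to known-groups differences unless the tests are also related to later CAIT. That link could be an optional exploratory analysis, for example 12-month CAIT regressed on each t1 or t2 test with adjustment for arm and baseline CAIT.

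For patients, these steps use measurements already scheduled, so the cost is analysis work. Fewer tests will look useful, and the arm-specific t2 comparisons rest on about 41 patients per arm instead of 82, so small deficits will be estimated less precisely.

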### Interim analyses [21b]

Not applicable.

### Methods for additional analyses (e.g., subgroup analyses) [20b]

Participant data will be split into age groups for additional analysis. Previous work of a retrospective analysis has been shown that there was the highest CAI rate in the oldest age group (14–25 years vs 26–40 years vs 41–55 years) [26]. Therefore, it might be of interest to see if this distribution changes by the training intervention and how age groups differ in functional parameters. Another possibility to divide subgroups is different levels of activity. It could be higher levels of activity might serve as a protection factor for developing a CAI.

### Methods in analysis to handle protocol non-adherence and any statistical methods to handle missing data [20c]

Again, statistical methods to handle non-adherence and missing data must be separated for the primary and secondary study aim:

#### Primary study aim

For the primary study aim, participants who withdraw from the study will excluded from statistical analysis.

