### Trial design [8]

This study will be a prospective, single-center, interventional randomized controlled trial with an active control group and a superiority framework. Furthermore, it will be unblended with the patient allocated in a 1:1 ratio to one of the two parallel groups.

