#### Adherence for NORMT

To improve adherence, the participants will get a financial compensation after 6 weeks (25 €) and 12 months (25 €), respectively.

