### Plans to promote participant retention and complete follow-up [18b]

As already mentioned in 11b, there are multiple strategies to promote the participant’s adherence to the intervention. There will also be check-ups during the 6-week-intervention. These are video calls which are attractive to the participant since they provide a low-threshold access to the intervention. These check-ups help to guide the intervention and eventually adapt it. The 6-month follow-up will be done via email with Heartbeat (service to collect questionnaires). By this, the participants can answer the questionnaires from home. Heartbeat will send reminders to the participant in case of not answering the questionnaire. There will be a list of all expected outcomes for the patients. The participants will get an expense allowance after 6 weeks and 12 months. By dividing disbursement of the expense allowance to the 6-week and 12-month time points, patients are further encouraged to complete their follow-up. In case a participant does not want to complete the follow-up, especially the diagnostic, we give the option to just complete the questionnaires via Heartbeat.

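### The randomised SMART versus NORMT comparison drops every participant who withdraws, which discards CAIT scores already given and leaves the primary result open to attrition bias of unknown size and direction

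*Protocol article*

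**What the plan says.** The section on non-adherence and missing data [20c] gives each study aim its own rule.

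- **Primary aim:** "participants who withdraw from the study will excluded from statistical analysis". Under Trial design [8] this aim belongs to an "interventional randomized controlled trial with an active control group and a superiority framework". Its outcome is CAIT before and after the 6-week intervention and at 6 and 12 months, compared as the difference in change between groups (Outcomes [12]) by repeated-measures ANOVA (Statistical methods [20a]).
- **Secondary aim:** "analysis will be conducted on an intent-to-treat basis, including data for each participant who was randomized, regardless of whether they later withdraw from the study". According to Objectives [7], this aim compares injured patients at t1 and t2 with an uninjured control group.

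No other section gives an all-randomised analysis set, a missing-data method or a sensitivity analysis for the primary aim. Two further sections bear on the point. Sample size [14] allows for 20% loss to follow-up. The retention section [18b] says that, for participants who do not want to complete the follow-up, "we give the option to just complete the questionnaires via Heartbeat".

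**The concern.** Withdrawal happens after randomisation and may depend on the treatment and on how the ankle is doing. Removing those who withdraw turns the randomised comparison into a comparison of those who stayed, and randomisation no longer guarantees that the two remaining groups are alike. The rule also throws away observed outcome data: someone who leaves after the 6-month questionnaire has given CAIT at t1, t2 and t3, and all three are lost.

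The protocol's own facts make it plausible that reasons for leaving differ by arm:

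- The interventions are not blinded [17a].
- SMART asks for five sessions a week for six weeks (5 × 6 = 30), while NORMT is physiotherapy if necessary.
- SMART participants receive 50 + 50 = 100 €, NORMT participants 25 + 25 = 50 €.

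At stake is whether the main conclusion on SMART reflects the treatment or reflects who remained.

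**Working it through.** **1. How many patients could be affected.** The plan's figures are 82 evaluable patients, 20% loss and 102 randomised. Check: 82 / 0.80 = 102.5, and 102 × 0.80 = 81.6, so 102 agrees with the plan to within rounding. If every planned loss were a withdrawal, about 102 − 82 = 20 randomised patients would leave the primary analysis. This is an upper bound, because the 20% is loss to follow-up in general. (Whether 82 follows from the stated effect size is a separate matter and is not used here.)

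**2. An assumed scenario.** The documents give no information on who leaves, so the following are assumptions: no true effect; 51 per arm; CAIT in SD units with correlation 0.5 between any two times; 20% lost in each arm after t2. SMART losses are those lowest on a variable whose correlation with the t2 score is r = 0.5, 0.8 or 1.0. NORMT losses are random.

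Dropping the lowest 20% of a standard normal variable raises the mean of the rest by φ(−0.842) / 0.80 = 0.280 / 0.80 = 0.35 SD. So among SMART completers the mean is shifted by

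- t2: 0.35 r
- t1, t3 and t4: 0.5 × 0.35 r = 0.175 r

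Mean shift over t2 to t4: (0.35 + 0.175 + 0.175) r / 3 = 0.233 r.

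| r | Bias, mean of t2–t4 (SD) | False positives, group effect | False positives, group by time |
|---|---|---|---|
| 0.5 | 0.12 | about 10% | about 6% |
| 0.8 | 0.19 | about 18–19% | about 9–11% |
| 1.0 | 0.23 | about 25–26% | about 11% |

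The bias column is 0.233 r. Simulation agrees with it and supplies the false-positive rates (nominal 5%).

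The group-by-time test suffers less because the baseline of the completers is shifted too. Relative to t1, the shift is 0.35 r − 0.175 r = 0.175 r at t2 and zero at t3 and t4, which averages 0.058 r over t2 to t4. Since the plan's contrast is the difference in change, the last column is the more relevant one.

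**3. Other assumptions on who leaves.**

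- Same loss and same mechanism in both arms: the shifts cancel and the bias is about 0.
- Poor scorers leave NORMT and SMART losses are random: the sign reverses, about −0.12 to −0.22 SD.

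**4. What a mixed model on all available scores achieves.** With the SMART losses of step 2, loss depends on scores that were observed or on chance, and the bias falls to within about 0.006 SD, with 5 to 6% false positives. If the same score-related loss in SMART comes before t2, the score that drives it is never seen. Adjusting for t1 with slope 0.5 then leaves

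- t2: 0.35 r − 0.5 × 0.175 r = 0.2625 r
- t3 and t4: 0.175 r − 0.0875 r = 0.0875 r
- mean: (0.2625 + 0.0875 + 0.0875) r / 3 = 0.146 r, which is 0.07 to 0.15 SD

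The training burden falls in this period, so the case is realistic and the model alone is not a full remedy.

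**The case against.** A reader might infer that the rule biases the result towards SMART. The documents do not support that. They say nothing on who withdraws or why, and the direction in step 2 comes from the assumption that only SMART loses poor scorers. The payment difference, taken alone, would favour retention in SMART. The objection stands in full on direction.

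The scope is also narrower than it may look:

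- The sentence covers withdrawal from the study. It does not exclude patients who merely stop training, and it is silent on a single missed questionnaire. A classical repeated-measures ANOVA would drop such a patient, but that follows from the method and may be settled in an analysis plan that is not shown.
- The questionnaire-only route and the reminders may keep withdrawals well below 20%. They do not change what happens to those who do withdraw.
- For the secondary aim, the protocol gives a sensible reason for keeping later withdrawals: t1 and t2 data remain usable. Calling this intention-to-treat is loose wording and does no harm there. It only shows that the principle was not applied where randomisation gives it meaning.

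It is tempting to measure the bias against a planned effect of 0.5 SD. The protocol states f = 0.5, which for two groups is 2 × 0.5 = 1.0 SD. No CAIT standard deviation is given, so the bias cannot be put in points or set against the 3-point MCID either.

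The exclusion cannot be excused as detail left to an analysis plan. The protocol fixes the rule, and a later plan could repair it only by contradicting it.

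**Conclusion.** The rule is wrong as written and should be changed before the data are analysed. It removes randomised patients because of a post-randomisation event, discards CAIT scores they have already given, and affects at most about 20 of 102 patients if losses run as planned. That conclusion rests on the text alone.

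The size and direction of any bias are unknown. The figures of 0.12 to 0.23 SD, with 10 to 26% false positives for the group effect and 6 to 11% for group by time, belong to one assumed one-sided mechanism. They show that the rule can do material harm, not that it will, nor that it would favour SMART.

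**What to change.** Replace the sentence for the primary aim in [20c] with wording such as: *All randomised patients are analysed in their allocated group, using every available CAIT score, in a likelihood-based mixed model for repeated measures.*

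In addition:

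- State that patients who stop training or decline the laboratory tests stay in follow-up through the questionnaire-only route already offered in [18b].
- Report the completers analysis as a sensitivity analysis only.
- Add a delta-adjusted sensitivity analysis, with the shift for missing scores varied separately in each arm because the direction is not known. It is needed because the mixed model removes the bias only if loss depends on observed scores.

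The cost is a few sentences of analysis wording, a mixed-model procedure in place of the ANOVA, and a little more analysis work. Recruitment, visits and sample size do not change.

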#### Secondary study aim

Since the secondary study aim is a cross-sectional analysis of t1 and t2, later withdrawal is irrelevant for the analysis. Therefore, analysis will be conducted on an intent-to-treat basis, including data for each participant who was randomized, regardless of whether they later withdraw from the study.

### Plans to give access to the full protocol, participant-level data, and statistical code [31c]

Data will not be released to any third party and will be analyzed independently by the study team. Data will be made available upon request to the primary investigator.

